**Table 1 T1:**
[figure not shown]
A detailed schedule of the trial.

### Case elimination and withdrawal criteria

2.10

#### Elimination criteria

2.10.1

The elimination criteria are as follows: case selection does not meet the inclusion criteria; it did not use the test drug; after the randomization, no data or major indicator missing, and the data is obviously incomplete; the drug prohibited by the test protocol was used, and the efficacy could not be evaluated.

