### Inclusion criteria

2.3

Patients will be enrolled in this trial if they meet the following criteria: there must be an informed consent form signed by the patient himself or by the witness; TNM III-IV GC or CRC; controlled by chemotherapy (CR/PR/SD); age 18 to 75 years (≥18 years’ old, ≤75 years’ old), expected survival period is >3 months; KPS ≥60^[28]^; follow the Response Evaluation Criteria In Solid Tumors (RECIST 1.1),^[29]^ at least 1 measurable lesion; routine blood test: hemoglobin ≥90 g/L; neutrophil count ≥1.5 × 10^9^ cells/L; platelet count ≥100 × 10^9^ cells/L; biochemical examination: total bilirubin ≤1.5 × upper limit of normal range (ULN), alanine aminotransferase (ALT) and aspartate aminotransferase (AST) ≤2× ULN, if liver metastasis, ALT and AST ≤5× ULN, endogenous creatinine clearance rate ≥60 mL/min; cardiopulmonary function is basically normal.

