### Interventions

2.7

In the S-1 group, S-1 was given orally twice daily at a dose of 80 mg/m^2^/d after a meal for 14 consecutive days, followed by 7 days of rest, and every 21 days counts as a cycle.

In the S-1 combined with XSLJZD group, S-1 was given orally twice daily at a dose of 80 mg/m^2^/d after a meal for 14 consecutive days, followed by 7 days of rest, and every 21 days counts as a cycle. According to the syndromes of the patients, XSLJZD was given combined treatment. The detailed composition of XSLJZD is as follows: Radix codonopsis 15 g, Rhizoma atractylodis macrocephalae 20 g, Poria 15 g, Pericarpium citri reticulatae 15 g, 10 g of Pinellia tuber, 10 g of Radix aucklandiae, 10 g of Fructus amomi, and 6 g of Radix glycyrrhizae.

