#### Primary endpoint

2.8.1

The primary endpoint is PFS, the time from randomization to disease progression (Evaluation of tumor progression about RECIST 1.1) or death.

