#### Secondary endpoints

2.8.2

The secondary endpoint is overall survival (OS) and Quality of Life Assessment (QOLA). OS is defined as the time from randomization to death for any reason. The last follow-up time is usually calculated as the time of death for the participants who have lost the visit before death (Additional file 1; Additional file 2; Additional file 3; Additional file 4).

QOLA, including symptom improvement, KPS, and AE assessment before and after treatment, was performed for 1 to 3 days before each cycle of treatment, Details are as follows:symptom improvement, mainly observe the changes of common symptoms of GC and CRC (pain, diarrhea, fatigue, poor acceptance, sleep), refer to the “Guiding Principles for Clinical Research of New Chinese Medicine” in the relevant TCM symptom integral quantification table of MDASI-TCM, compared to the scores accumulated for each symptom, analyze the difference before and after treatment^[30]^; KPS, comparative analysis before and after the difference; assessment of AE (safety outcomes). Assessment and grading of AE were based on the Common Terminology Criteria for Adverse Events (CTCAE) Version 4.0,^[31]^ AEs include nausea and vomiting, granulocytopenia, thrombocytopenia, anemia, impairment of liver and kidney function, diarrhea, peripheral neuritis, stomatitis, hand-foot syndrome, and any other new symptoms or diseases related to or unrelated to intervention. SAEs refer to the events that must be hospitalized or prolonged, permanently and seriously disabled, life-threatening, or death in clinical trials. SAE will be reported to the chief researcher and the hospital ethics committee, and the experiment will be stopped within 24 hours.

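### Section 2.10.1 eliminates randomised patients on post-randomisation grounds, and nothing in the protocol states that PFS and OS are compared in all patients as randomised

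*Protocol article*

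**What the plan says.** Section 2.10.1 (Elimination criteria) lists four grounds:

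- Ineligibility: "case selection does not meet the inclusion criteria".
- Non-use of treatment and missing data: "it did not use the test drug; after the randomization, no data or major indicator missing, and the data is obviously incomplete".
- Prohibited medication: "the drug prohibited by the test protocol was used, and the efficacy could not be evaluated".

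Withdrawal is a separate list (2.10.2). Section 2.10.3 deals with patients who do not attend and patients who ask to stop. Their data are kept, follow-up continues, and survival status is tracked where the patient allows it.

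Both time-to-event endpoints start at randomisation: "The primary endpoint is PFS, the time from randomization to disease progression" (2.8.1) and "OS is defined as the time from randomization to death for any reason" (2.8.2). Section 2.13 gives medians by group, Kaplan–Meier curves and the log-rank test, and names no analysis population.

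Both arms take S-1. Only one arm also takes the decoction: "According to the syndromes of the patients, XSLJZD was given combined treatment" (2.7). Section 2.1 and the Discussion describe the trial as open, while 2.6 says that clinicians, patients and assessors are blinded.

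**The concern.** Randomisation makes the arms comparable at time zero. A rule that drops patients on later information (whether they took treatment, whether their data are complete, what else they took) can undo this if the patients dropped differ in prognosis or number between the arms.

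Two features of this trial make unequal elimination plausible. First, only the combination arm can fail to take the decoction. If the test drug in 2.10.1 means XSLJZD, S-1 patients cannot meet that ground at all. Second, if the trial is open, as 2.1 says, a judgement that efficacy could not be evaluated may be made with the arm known. The independent committee described under Protocol monitoring evaluates imaging under blinding, but the text does not give it the elimination decisions.

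At stake is who enters the comparison on the primary endpoint. The rule is also unnecessary for a time-to-event endpoint: incomplete follow-up is handled by censoring, and a patient who took no drug still has a PFS and an OS time.

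**Working it through.** **1. Does any passage restore eliminated patients?**

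| Section | Content | Restores them? |
|---|---|---|
| 2.8.1, 2.8.2 | PFS and OS timed from randomisation | No; defines the clock, not the population |
| 2.10.2 | Withdrawal from treatment or study | No; a different category |
| 2.10.3 | Data and follow-up kept for non-attenders and patients who ask to stop | Not for eliminated cases |
| 2.13 | Medians by group, Kaplan–Meier, log-rank | No; no population named |

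**2. The plan's own figure.** Section 2.12 gives two-sided α = 0.05 (sidedness from 2.13), power 80%, SD 9.59, 10% dropout and 64 per group, but no target difference. The figure therefore cannot be reproduced from stated inputs. With an assumed difference of 5 points, n = 2 × (1.96 + 0.84)² × 9.59² / 5² ≈ 57.7, so 58 per group. Then 58 / 0.9 gives 65 and 58 × 1.1 gives 64. The present point does not depend on this. If the whole dropout allowance were eliminated, about 0.9 × 256 ≈ 230 patients would be analysed, or about 115 of 128 per carcinoma type.

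**3. Illustration A: early failures removed.** Assumptions, none from the document: no true effect, exponential PFS with median 6 months in both arms, no censoring, and a stated share of patients with an event before a cut-off removed. If half are removed, the fraction of the arm lost is 0.5 × (1 − 2^(−c/6)). For c = 1.5 months this is 0.5 × 0.159 = 8.0%; for c = 2 months it is 0.5 × 0.206 = 10.3%. The last column is the chance of a log-rank result at two-sided 5% that favours the combination (nominal 2.5%). Each scenario used 3,000 to 4,000 simulated trials at 128 per arm, and ranges cover repeated runs.

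| Share removed, combination / S-1 | Cut-off | Apparent HR | Favourable false positives |
|---|---|---|---|
| 0 / 0 | – | 1.00 | 2.4–2.5% |
| 50% / 50% | 2 months | 1.00 | 2.5% |
| 50% / 25% | 1.5–2 months | 0.96–0.95 | 4.9–6.5% |
| 25% / 0 | 2 months | 0.95 | 5.7% |
| 50% / 0 | 1.5 months | 0.92 | 8.5–9.3% |
| 50% / 0 | 2 months | 0.90 | 12.1–12.7% |

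At 64 per arm (one carcinoma type alone), the two 50% / 0 scenarios give about 6–9%.

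**4. Illustration B: a higher-risk subgroup removed from one arm.** A fraction f of each arm has h times the hazard, and it is removed from the combination arm only. With no true effect, the ratio of mean times is f/h + (1 − f) = 1 − f(1 − 1/h).

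- f = 0.05, h = 1.5: 1 − 0.05 × 0.333 = 0.98.
- f = 0.15, h = 3: 1 − 0.15 × 0.667 = 0.90. The simulation at 64 per arm, where rounding removes 10 of 64, gave 0.89.

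Two-sided type I error over f = 5–15% and h = 1.5–3 was about 5–10% at 64 per arm and 5–12% at 128 per arm, against 5% with no elimination.

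**The case against.** The strongest reply has five parts.

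- **The exclusion is inferred.** The article never says that eliminated cases leave the PFS or OS analysis, and analysis sets are often left to a statistical analysis plan, which is not shown here. It is right that a reader might take 2.10.1 as an express statement that PFS and OS will not be compared as randomised; the text does not go that far. But elimination is set apart from withdrawal, and its ordinary meaning is removal from the evaluated cases. The protocol itself fixes this rule, so it is more than detail left out.
- **The grounds are narrower than they first look.** The missing-indicator ground is joined to obviously incomplete data, and the prohibited-drug ground applies only where efficacy could not be evaluated. Both qualifiers stand. They limit how many patients are affected, but they remain judgements made after randomisation.
- **Illustration A is not the rule itself.** A recorded progression or death is the primary endpoint, so it is not a missing indicator. This stands. The scenario can only stand in for poor-prognosis patients who took no drug or were lost before any assessment, and its 50% share has no basis in the text.
- **Unequal action by arm is not stated.** All four grounds can apply to both arms if the test drug means S-1, and the syndrome-based use of the decoction is not linked to elimination. Equal elimination at equal prognosis gives no bias. The 10% dropout in 2.12 is an overall figure, not 10% in one arm and none in the other.
- **Section 2.10.3 helps in part.** It protects patients who stop or miss visits. It does not reach those who are eliminated.

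A reader might also infer that patients in complete response will be enrolled and then eliminated, because 2.3 admits patients "controlled by chemotherapy (CR/PR/SD") and also asks for "at least 1 measurable lesion". The document does not support this. It does not say which scan the lesion criterion refers to, and on a strict reading such a patient would fail screening. This is a separate eligibility ambiguity.

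**Conclusion.** The concern holds in this form: 2.10.1 sets a rule that, read in the ordinary way, takes randomised patients out of the PFS and OS comparison on post-randomisation information, and no passage states an as-randomised analysis. The unresolved open-versus-blinded description and the decoction in one arm only raise the risk that elimination is unequal.

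The document does not allow the size or direction of bias to be determined. A reader might conclude that the plan will make an ineffective add-on look effective, but that needs poor-prognosis patients to be removed mainly from the combination arm, which is an assumption. The illustrative range runs from no bias (HR about 1.00, favourable false positives 2.5%) when elimination is balanced, through apparent HRs of about 0.98 to 0.89 in one-sided or unequal scenarios. At its upper end the favourable false-positive rate is 12–13% at 128 per arm, or about 6–9% at 64 per arm in the one-sided early-failure scenarios. Removal concentrated in the S-1 arm would push the estimate the other way.

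**What to change.** State in 2.13 that the primary analyses of PFS and OS include all randomised participants in the arm assigned, whatever treatment they took, with censoring where follow-up ends. Reword 2.10.1 so that its criteria only define a secondary per-protocol set.

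Separately, reconcile the response categories and the measurable-lesion wording in 2.3 by saying which scan the lesion criterion refers to.

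The cost is a rewording. No new patients or visits are needed, and the planned 256 (64 per group in each carcinoma type) is unchanged. The downside is a slight dilution of the estimated effect from patients who never take the treatment.

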#### Withdrawal criteria

2.10.2

The withdrawal criteria are as follows: participants voluntarily request to withdraw from the test; SAE closely related to drugs occur, and toxicity intolerance makes the test impossible to continue; no reason for delaying treatment for >2 weeks; it cannot be treated according to the program, poor compliance; considering the interests of the participants, the researchers believe that the best choice is to terminate the study treatment.

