### Follow-up

2.9

This study is expected to last for 5 years. Each patient will be followed until death or withdrawal from the study. Follow up frequency: follow up every 28 ± 3 days in the first year of the study, and record the PFS; then follow-up every 3 months and record the OS of 3 year and 5 year.

A detailed schedule of the study is presented in Table 1.

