#### Solution

2.10.3

If the participant does not appear as planned during the follow-up period, the researcher shall know the reason as much as possible, record the reason on the case report form (CRF), contact the participant as much as possible to ask the participant to conduct a final visit, record the last medication time, try to complete the effectiveness and safety inspection when withdrawing from the study as specified in the scheme, and complete the safety follow-up period. AE and outcomes were fully recorded. According to the actual situation of the participants, researchers can suggest or provide new or alternative treatment methods to the participants.

If the participant is asking for termination of the study, researchers will retain the data and must follow-up in the specific follow-up steps specified in the study. If the participant refuses to visit further, he or she should continue to track his or her survival status unless the participant refuses to disclose further information or is contacted. In this case, no further research evaluations should be conducted, and no further information should be collected. The study sponsor may retain and continue to use all the information before the withdrawal of the participant's informed consent, unless the participant requests that the collected information be withdrawn.

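### Stopping treatment is classed as study withdrawal, and follow-up is said to end at withdrawal, so PFS and OS may be cut short for reasons linked to prognosis

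*Protocol article*

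**What the plan says.** All references are to the protocol article.

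- **Section 2.10.2 (Withdrawal criteria)** lists four grounds next to a participant's own request to leave. One is toxicity: "SAE closely related to drugs occur, and toxicity intolerance makes the test impossible to continue". Another is an unexplained gap in dosing of more than two weeks. A third is adherence, worded as "it cannot be treated according to the program, poor compliance". The last is the case where, in the participant's interest, "the researchers believe that the best choice is to terminate the study treatment". This last item shows most clearly that ending treatment is counted as withdrawal.
- **Section 2.9 (Follow-up)**: "Each patient will be followed until death or withdrawal from the study".
- **Section 2.10.3 (Solution)**: "If the participant is asking for termination of the study, researchers will retain the data and must follow-up in the specific follow-up steps" laid down by the study. Survival status is still tracked for someone who refuses visits, unless that person also declines to give further information. For missed visits it asks for contact, a final visit and safety follow-up.
- **Sections 2.8.1 and 2.8.2** run PFS from randomisation to progression or death, and OS from randomisation to death from any cause. Neither endpoint ends when treatment stops.
- **Section 2.8.2** adds a rule for OS: "The last follow-up time is usually calculated as the time of death for the participants who have lost the visit before death".
- **Section 2.13** analyses both endpoints with Kaplan-Meier curves and the log-rank test.

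**The concern.** Read together, sections 2.10.2 and 2.9 end outcome follow-up for a patient whose treatment is stopped for toxicity, unexplained delay, poor adherence or the investigator's judgement. These reasons can be linked to prognosis. Kaplan-Meier and log-rank methods assume that censoring carries no information about the later event. If patients who leave early have a higher hazard, and more leave one arm than the other, the remaining comparison is no longer quite the randomised one.

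Unequal withdrawal is plausible both ways. The Introduction reports that the herbal formula eases chemotherapy side effects, which would mean fewer toxicity withdrawals in the combination arm. Section 2.7 gives that arm an eight-herb decoction in addition to S-1, which could mean more adherence withdrawals. Outcome data not collected during the trial cannot always be recovered afterwards, so this belongs in the protocol.

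**Working it through.** **1. The text, by type of exit**

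| Patient | Section 2.9 | Section 2.10.3 | Result |
|---|---|---|---|
| Asks to leave | follow-up ends | follow-up continues | direct conflict |
| Misses visits | not addressed | contact, final visit, safety follow-up | partly covered |
| Withdrawn by investigator (toxicity, delay, adherence, judgement) | follow-up ends | not named | only 2.9 plainly applies |

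**2. Size of the effect**

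The plan gives no withdrawal rate by arm and no figure for this point, so there is nothing to reproduce. Section 2.12 gives only a 10% overall dropout and 64 patients per group for each cancer; section 2.6 gives 1:1 allocation. I assumed a split of 5% v 15%, which is consistent with that overall rate: (5% + 15%)/2 = 10%. Per group of 64 this is 0.05 × 64 = 3.2 and 0.15 × 64 = 9.6 patients.

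*PFS, all inputs assumed.* Exponential times, median 8 months; 30% of patients with 2 to 3 times the hazard of the rest; withdrawals drawn from that 30%, at 0-3 months, and censored there; true hazard ratio 1. Estimated Cox hazard ratio, combination to S-1:

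- 5% v 15% (S-1 v combination): about 0.94-0.97.
- 15% v 5%: swapping the arms inverts the ratio, so 1/0.97 = 1.03 to 1/0.94 = 1.06. Simulation runs of this case gave values from 1.03 to 1.06, most of them near 1.03-1.04.
- Equal rates: about 0.99-1.00.
- Follow-up continued after withdrawal: about 1.00, whatever the split.

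*OS, if withdrawn patients are also handled as lost under section 2.8.2.* Assumed median 12, 18 or 24 months, 36 months of follow-up, withdrawal at 0-12 months counted as death:

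- 5% v 15%: about 1.09-1.15.
- 15% v 5%: by inversion, 1/1.15 = 0.87 to 1/1.09 = 0.92. Simulation runs lay between 0.88 and 0.92.

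In this OS model withdrawal is unrelated to prognosis, and censoring the same patients at the same times leaves the ratio at about 1.00. The OS shift shown here therefore comes from counting them as deaths.

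**3. Against the noise**

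With an assumed 90-110 PFS events per cancer, the standard error of the log hazard ratio is about 2/√D: 2/√90 = 0.21 and 2/√110 = 0.19. The PFS shifts are |ln 0.97| = 0.030 and |ln 0.94| = 0.062, that is 0.030/0.21 = 0.14 to 0.062/0.19 = 0.33 of a standard error.

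**The case against.** The best defence is that section 2.10.3 is the operative rule for the whole of section 2.10. If even a participant who asks to leave must be followed, then a patient taken off treatment for toxicity or adherence should be followed all the more. The general sentence in section 2.9 can then be read as meaning the point at which no further information may be collected. The schedule table, the flowchart and the additional files are also not visible, and no sentence says that PFS is censored at withdrawal.

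Part of this stands. It is a reasonable reading and perhaps the intended one, so a reader should not infer that the plan certainly discards these outcomes. But it has to be supplied by inference. As written, section 2.9 ends follow-up at withdrawal, section 2.10.2 calls these patients withdrawn, and the continuation rule is triggered only by a participant's request. The gap comes from stated text, not from detail that an article leaves out.

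Three stronger readings are tempting and not supported:

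- *That the decoction's daily burden makes withdrawal higher in the combination arm.* Section 2.7 gives herb weights but no frequency, and the Introduction's toxicity rationale points the other way. The direction is unknown.
- *That the randomised comparison is lost.* The PFS shift is a fraction of a standard error under these assumptions, and negligible with equal rates. Larger shifts need wider gaps in withdrawal or a closer tie between the time of leaving and the event than the documents suggest.
- *That the withdrawal wording itself turns living patients into OS deaths.* That effect comes from the rule in section 2.8.2, which concerns patients lost to visits and is qualified by the word for usual practice. Whether it would be applied to withdrawn patients is not stated.

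**Conclusion.** The point holds in conditional form. Sections 2.9 and 2.10.3 conflict for participants who ask to leave, and for patients withdrawn by the investigator only section 2.9 plainly applies. If it is followed, PFS and OS are truncated for reasons that may be informative and may differ by arm. The likely bias in PFS is modest, a few per cent on the hazard ratio in either direction, and it rests on assumed withdrawal rates, timing and prognosis. The larger and opposite OS shift arises only if the last-visit-as-death rule is also applied to these patients. The text should be reconciled because the flaw is easy to remove and touches the primary endpoint, not because a large bias has been shown.

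**What to change.** Reconcile sections 2.9, 2.10.2 and 2.10.3:

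- Split section 2.10.2 into *discontinuation of study treatment* (toxicity, unexplained delay, adherence, investigator's decision) and *withdrawal of consent to follow-up*.
- Reword section 2.9 so that every randomised patient is followed for progression and death until death, withdrawal of consent or the data cut-off, whatever treatment is received.
- Name investigator-initiated discontinuations in section 2.10.3, so that its continuation rule covers them.
- Censor patients who are truly lost at last contact, and do not count them as deaths in OS.

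The cost is amendment wording plus some further assessments or survival contacts after treatment stops. Section 2.10.3 already foresees survival tracking, so the added burden is limited. The change concerns outcome collection only and takes no position on when treatment should stop.
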